## 5. TREATMENT OF SUBJECTS

### 5.1 Non-investigational product/treatment

Volunteers will be exposed to a predefined dose of female cercariae according to the schedule depicted in figure 1, by applying female cercariae to the intact skin of the forearm for 30 minutes. Cercariae will be applied to the skin in 0.5-1.0 ml Bar-le-duc water. Every volunteer will be exposed to cercariae once.

### 5.2 Use of co-intervention

Severe itching at the site of entry of the larvae (swimmer's itch) may be treated with triamcinolone cream 0.5% (applied twice daily) according to local clinical practice [13]. In case of symptoms of acute schistosomiasis syndrome (Katayama fever), subjects will receive symptomatic treatment such as paracetamol or, in case of severe symptoms lasting more than 48 hours, NSAIDs or oral prednisone in doses up to 30 mg. Dosing and administration of these drugs or any other symptomatic drugs will be determined according to severity and duration of the adverse events. Female volunteers are requested to use adequate contraception. There are no dietary requirements.

### 5.3 Escape medication

The trial physician may decide to abrogate the study for individual subjects according to the criteria described in section 8.4. Because early treatment of schistosomiasis infection has been shown to aggravate clinical symptoms in reported cases, the advantages and disadvantages of such escape medication should be carefully weighed. Escape medication should, in symptomatic cases, be accompanied by symptomatic treatment with corticosteroids.

Escape medication to abrogate the study for individual volunteers before week 8 of the study will be artemether/lumefantrine in a standard 6-dose treatment regimen over 3 days. Volunteers with early abrogation of infection are also treated with praziquantel 60 mg/kg at week 8.

## 6. NON-INVESTIGATIONAL PRODUCT: female cercariae

### 6.1 Name and description of non-investigational product(s)

Volunteers will be exposed to a predefined dose of female cercariae according to the schedule depicted in figure 1, by applying female cercariae to the intact skin of the forearm for 30 minutes. Every volunteer will be subjected to one exposure to cercariae. For details on the production and quality control of these female cercariae, please refer to the Product Dossier section 2.1.P.3 “Manufacture” and 2.1.P.5 “Control of the cercarial product”.

### 6.2 Summary of findings from non-clinical studies

Please refer to the Product Dossier section 2.2 “Non-clinical data and toxicology”.

### 6.3 Summary of known and potential risks and benefits

Please refer to the Product Dossier section 2.4 “Overall risk and benefit assessment”. In addition, a structured risk analysis is given in chapter 13 of this protocol.

### 6.4 Description and justification of route of administration and dosage

Female cercariae will be allowed to penetrate the skin of human volunteers by applying 0.5-1 ml of Bar-le-duc water containing the specified number of cercariae on the skin for 30 minutes. This route has been chosen because it is the natural route of infection and complications of the site of entry other than swimmer’s itch have not been described. From non-human primate and rodent experience we expect roughly 5-70% of cercariae to develop into mature worms after penetration of the skin. Also from rodent experiments we expect that female cercariae will not fully mature because they are not able to mate. As such, they will produce less CAA as compared to the same number of mixed-sex infections. We extrapolated that we would need roughly 5 mature female worms to be able to potentially detect circulating CAA. Because not all cercariae may penetrate the skin we chose 10 cercariae as the minimal dose for controlled human infection that may possibly be detectable in a number of volunteers, which is the same starting dose as for the single-sex infection with male *Sm*. The dose-escalation scheme as shown in figure 1 takes into account that 1) fewer female worms may reach maturity and 2) CAA may be lower than in mixed-sex or single-sex male infections.

### 6.5 Dosages, dosage modifications and method of administration

Doses of cercariae will be prepared by manual counting and checked by a second technician. Cercariae will be administered by natural penetration of the skin in 0.5-1 ml of Bar-le-duc water.

## 6.6 Preparation and labelling of Non Investigational Medicinal Product

Cercariae will be prepared in the A1 well of a 24-well plate. The plate will be labelled with the following sticker, which will be completed at the time of preparation:

FEMALE CERCARIAE for the purpose of CoHSI

Trial identifier: CoHSI2

Snail identifier:

Total number:

Well:

Date:

Time end shedding:

Time plate ready:

Do not use after: (time)

Name technicians:

Signatures:

For the purpose of medical research only

## 6.7 Drug accountability

After controlled human schistosomiasis infection, the number of tails, heads and intact cercariae will be counted under the microscope (of the A1 well of the 24-well plate, of the water on the forearm of the volunteer, and of the rinsing water used for each volunteer).

Numbers will be noted in the clinical trial database. All equipment used is disposable and will be destroyed according to biosafety level 2 regulations.

## 7. NON-INVESTIGATIONAL PRODUCT: praziquantel

### 7.1 Name and description of non-investigational product(s)

#### Praziquantel

All volunteers will be treated with 60 mg/kg praziquantel at week 8 and week 12 after infection. Praziquantel is the only drug registered for the treatment of schistosomiasis. Cure rates with a single dose of 40 mg/kg has been reported to vary between 40-90% [4, 5] in endemic areas, however in travelers the efficacy appears lower [14] which may be caused by lower infection intensity or differential host-immune responses. Therefore, repeated praziquantel doses may be required to achieve full cure. A common side effect of praziquantel (>10%) is fatigue. Other less common side effects are abdominal discomfort, nausea, and dizziness. For a summary of findings from non-clinical and clinical studies, please refer to the “bijsluiter” (SPC Praziquantel). Praziquantel has been described to temporarily impair skilled tasks, and thus volunteers treated with praziquantel will be advised not to drive a car or operate machinery on the day of treatment with praziquantel and the day thereafter [15]. They are instructed to take praziquantel after a meal preferably containing high-fat, and high carbohydrate content [16].

### 7.2 Dosages, dosage modifications and method of administration

The dose administered will be 60 mg/kg praziquantel, split into two doses during one day. This dose is higher than the 40 mg/kg dose recommended by WHO for preventive chemotherapy in endemic settings. We chose the 60 mg/kg dose because of two reasons. Firstly, meta-analysis by Zwang *et al.* suggested that cure rates with single-dose 60 mg/kg were slightly higher than with single-dose 40 mg/kg (84.6% vs. 76.7%, respectively), however confidence intervals around the estimates were overlapping [17]. Secondly, in mice the EC for single-sex female infections appeared to be higher than for single-sex male or mixed-sex infections [18].

In addition to treatment at week 8, all volunteers will receive a second round of treatment at week 12 to ensure that any previously immature worms, that were less susceptible to praziquantel at week 8 [18], are also killed.

Although more recently, WHO advises a single-dose in MDA to improve uptake, splitting the dose in our study (i.e. two doses during one day) may reduce risk of side effects.

Praziquantel will be taken after a meal.

### 7.3 Preparation and labelling of Non Investigational Medicinal Product

Praziquantel will be prepared and labelled for individual volunteers according to the standard procedures in the treatment of schistosomiasis. Each volunteer will receive exactly the calculated number of tablets calculated on weight basis:

| 60 mg/kg dose |                                 |
|---------------|---------------------------------|
| Weight (kg)   | Number of tablets (600 mg each) |
| 48-52         | 5                               |
| 53-57         | 5½                              |
| 58-62         | 6                               |
| 63-67         | 6½                              |
| 68-72         | 7                               |
| 73-77         | 7½                              |
| 78-82         | 8                               |
| 83-87         | 8½                              |
| 88-92         | 9                               |
| 93-97         | 9½                              |

### 7.4 Drug accountability

Praziquantel tablets are dispensed by the hospital pharmacy in containers with 6 tablets. The exact number of tablets of praziquantel will be distributed to the volunteers by the clinical investigator. Remaining tablets will be returned to the pharmacy for destruction according to appropriate regulations. A drug accountability log will be kept through signature lists at the trial site. These records will include:

- volunteer identification number;
- number of tablets dispensed and remaining;
- signature of the clinical investigator dispensing the tablets.

## 8. METHODS

### 8.1 Study parameters/endpoints

#### 8.1.1 Main study parameter/endpoint

- Frequency and severity of adverse events after controlled human *Schistosoma mansoni* infection with female cercariae
- The number of female cercariae at which 100% volunteers show detectable *Schistosoma mansoni* circulating anodic antigen

#### 8.1.2 Other study parameters/endpoints

- Time to positive serum and urine CAA test
- Comparison of the peak serum CAA concentration in different dose groups
- Humoral (antibody) response directed against *Sm* antigens
- Cellular responses directed against *Sm* antigens
- Changes in microbiome after controlled human *Schistosoma mansoni* infection with female *Sm* cercariae

### 8.2 Randomisation, blinding and treatment allocation

The trial will be an open label trial, so there will be no randomisation or blinding procedure.

### 8.3 Study procedures

#### Recruitment of volunteers

Advertisements will be placed in prominent places on the university and hospital campuses and other public places as well as on the internet and intranet site of the LUMC. Furthermore, a Facebook page showing the advertisement text will be designed to inform people about the trial. The study will be advertised on social media. This brief advertisement will indicate a telephone number to call and an e-mail address for contact to request further information. It will furthermore indicate a website ([www.vaccinonderzoek.nl](http://www.vaccinonderzoek.nl)) which contains a form to request further information. We will also reach out to people via email to people who have subscribed to our newsletter. All volunteers with interest in participation in the study will be advised to join one of the information meetings and will receive the study documents (the information sheet, the application form and the insurance text about the study. If they are still interested after the meeting or after reading the documents, an appointment for a screening visit will be made.

The screening visit will be planned at least 72 hours after the subject receives the information sheet and informed consent form.

### **Screening visit**

During the screening visit, volunteers are first given the opportunities to address any study related questions after which they will be asked to sign the informed consent form if they still want to participate. All volunteers must consent to an HIV, hepatitis B, hepatitis C serological screening, urine toxicology and for females a pregnancy test at screening. A copy of the informed consent form will be given to the volunteer. Subsequently volunteers are asked to complete an application form which includes a questionnaire regarding their health. The questionnaire answers will be discussed and inclusion and exclusion criteria will be checked. The possibility of withdrawal from the infection study, at any time and without any declaration of the reason as well as the resulting necessary follow-up visits for safety will be pointed out to the volunteers. All volunteers will be asked to supply a phone number of a person who may be contacted in case of emergency.

A physical examination will be performed, including the examination of general appearance, skin, neck, eyes, throat, lungs, heart, abdomen, back and extremities, and a routine vascular and neurological examination. Vital signs (tympanic temperature, blood pressure (BP) and pulse) will be measured.

Height (cm) and body weight (to the nearest kilogram [kg] in indoor clothing, but without shoes) will be measured at the screening visit. Body mass index (BMI) will be calculated using the following formula:  $BMI = \text{Body weight (kg)} / [\text{height (m)}]^2$ .

### **Infection with female *Sm* cercariae**

At the day of exposure to female *Sm* cercariae, volunteers will visit the clinical trial centre in the morning for a final check of in- and exclusion criteria, a focussed physical exam and vital signs. Blood will be drawn for baseline assessments and safety lab will be checked.

In the afternoon, exposure to female *Sm* cercariae will be performed at the laboratory of the parasitology department (P4) within the LUMC building 1. Female cercariae will be allowed to penetrate the skin of human volunteers by applying 0.5-1ml of Bar-le-duc water containing the specified number of cercariae on the skin for 30 minutes.

Exposures will be performed by one of the clinical investigators. A nurse or second investigator will be present to check study procedures. Volunteers will be observed for at least 30 minutes after the exposure.

### **Follow-up after infection**

Volunteers will visit the trial centre for screening, then at the day of infection and every week starting from 1 week after infection until 16 weeks after infection. After week 16, biweekly follow-ups will follow until week 20. Final visit will be performed at 1 year after infection. At all follow up visits, adverse events will be recorded, volunteers will undergo a blood draw by venepuncture and will provide a urine sample. At every visit the tympanic temperature will be checked (until week 12). A focused physical examination will be performed if deemed necessary by the trial physician. Volunteers are requested to keep a diary from the day of infection until 20 weeks, in which they record adverse events. A clinical trial physician will be available by mobile phone 24/7 during the 20 weeks clinical trial period. Volunteers will be instructed to report to the clinical trial physician in case of any grade 2 (moderate) or grade 3 (severe) adverse events to ensure early detection and possible treatment of symptoms of acute Schistosomiasis infection (see paragraph 9.2.4 [Adverse events data collection](#) for more detailed information).

Additional diagnostics (including serum CAA tests) can be performed on discretion of the trial physician at any time if it is deemed necessary for the safety of the study volunteers.

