### **Recording of adverse events**

Signs and symptoms will be recorded at all visits and whenever a trial volunteer reports signs or symptoms to the trial physician between visits. The following signs and symptoms will be solicited at all visits: itching, fever (by examination), rash, urticaria, headache, fatigue, malaise, coughing, myalgia, arthralgia, night sweats, back pain, anorexia, nausea, vomiting, abdominal pain, diarrhoea.

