### 8.7 Premature termination of the study

The study may be discontinued for one of the following reasons:

- a serious adverse event which is possibly, probably or definitely related to the infection with female *Schistosoma mansoni* cercariae;
- >50% of subjects in a dose group (more than 1 out of 3 from group A or more than 5 out of 10 from groups A and B) experience a grade 3 adverse event, possibly, probably or definitely related to infection with female *Schistosoma mansoni* cercariae and persisting at grade 3 for >48 hours during the 20 weeks follow-up;
- on advice from the SMC;
- on advice from the investigator, pending discussion with the SMC;
- on advice from the accredited METC.

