#### **9.2.4 Adverse events data collection**

Safety assessments will be performed, and recorded by the investigators. All adverse events/reactions (solicited and unsolicited), observed by the investigators or by the subject, will be accurately documented in the case report form by the investigators.

For each event/reaction the following details will be recorded:

1. Description of the event(s)/reaction(s)
2. Date and time of occurrence
3. Duration
4. Intensity
5. Relationship with the intervention
6. Action taken, including treatment
7. Outcome

Symptoms will be ranked as (1) mild, (2) moderate, or (3) severe, depending on their intensity according to the following scale:

- Mild (grade 1): awareness of symptoms that are easily tolerated and do not interfere with usual daily activity
- Moderate (grade 2): discomfort that interferes with or limits usual daily activity
- Severe (grade 3): disabling, with subsequent inability to perform usual daily activity, resulting in absence or required bed rest

For fever, the following scale will be used:

- Mild (grade 1): 37.5 - 38.0°C
- Moderate (grade 2): > 38.0 to 39.0°C
- Severe (grade 3): > 39.0°C

Temperature will be measure tympanically.

If an AE changes in frequency or intensity during the specified reporting period, these changes will be documented in the eCFR. The highest severity grade will be noted in the eCFR.

When an AE/SAE occurs, it is the responsibility of the investigators to review all documentation (e.g. hospital progress notes, laboratory, and diagnostics reports) related to the event. The investigators will then record all relevant information regarding an AE/SAE on the eCRF or SAE Report Form, respectively.

The investigator will attempt to establish a diagnosis of the event based on signs, symptoms, and/or other clinical information. In such cases, the diagnosis should be documented as the AE/SAE and not the individual signs/symptoms.

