## 10. STATISTICAL ANALYSIS

### 10.1 Primary study parameter(s)

#### 10.1.1 Frequency and severity of adverse events

All volunteers exposed to female *Sm* cercariae will be included in the intention to treat analysis. The safety and tolerability of controlled infection with female *Sm* is evaluated by tabulating all adverse events for each volunteer in an intention to treat analysis. Adverse events will be analysed by calculating the proportion of volunteers in each group who reported mild, moderate or severe adverse events. Given the very small group size, adverse events will mostly be descriptive. If relevant, statistical testing will be performed using chi-square tests or Fisher's exact tests.

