*Schistosoma mansoni* worms reproduce sexually within the human host. A pair of male-female adult worms is able to produce hundreds of eggs per day [21]. However, worms do not multiply within the human host. Thus, a self-amplifying mechanism is highly unlikely. If an egg would accidentally be excreted into the environment through contaminated faeces, the life cycle *Schistosoma mansoni* would be unable to continue in the absence of the intermediate host, *Biomphalaria* snails, in The Netherlands, and adequate sanitation.

b. Previous exposure of human beings with the test product(s) and/or products with a similar biological mechanism

Controlled infections with female *Schistosoma mansoni* cercariae have not been performed in humans before, however we do have experience with controlled infection with male *Schistosoma mansoni* cercariae. We expect the symptoms related to the female worm maturation to be similar or less than those of the male worm maturation. This is supported by data from mice experiments that suggest the sex of cercariae differentially impacts host immune responses: infection with female cercariae appear to dampen host immune responses [12]. Consequently, symptoms associated with upregulated immune responses to worms, may be less apparent in female-only infections. In contrast with the male-only infection, in the female-only infection there is a small risk of egg-related symptoms. Please refer to paragraph 11.3 or the Product Dossier section 2.3.2 :“Human exposure” for a detailed description of clinical syndromes associated with *Schistosoma mansoni* infection. In brief, the percutaneous penetration of cercariae may provoke a temporary urticarial rash which is usually discreet, limited to the site of entry and rarely requires medical attention [6]. Acute schistosomiasis syndrome (Katayama fever) is a systemic hypersensitivity reaction against the migrating schistosomulae, *Schistosoma* eggs or both, which occurs three to ten weeks after infection [6, 7, 21, 24-26]. The disease presents with fever, fatigue, myalgia, malaise, non-productive cough, eosinophilia and patchy infiltrates on chest radiography [21, 24-26]. Most patients recover spontaneously after 2-10 weeks. In our earlier study, acute schistosomiasis syndrome was more frequently observed in the higher dose group (30 cercariae) suggesting dose-dependency [11].

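### Fever is graded only by tympanic temperature, but routine readings are weekly, end at week 12, and no between-visit measurement is specified

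*Protocol*

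**What the plan says.** The first main endpoint in section 8.1.1 is "Frequency and severity of adverse events after controlled human" infection with female cercariae. Section 10.1.1 analyses it by "calculating the proportion of volunteers in each group who reported mild, moderate or severe adverse events". The grade given to each event therefore feeds a primary result directly.

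Section 9.2.4 grades most symptoms by their effect on daily activity but treats fever separately: "For fever, the following scale will be used". Grade 1 is 37.5 to 38.0 °C, grade 2 is above 38.0 to 39.0 °C, and grade 3 is above 39.0 °C. The method follows: "Temperature will be measure tympanically". It does not say who measures, or where.

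Section 8.3 (Follow-up after infection) sets visits weekly to week 16, then at weeks 18 and 20, then at one year. On temperature it says: "At every visit the tympanic temperature will be checked (until week 12". Volunteers keep an adverse event diary to week 20, are told to report any grade 2 or 3 event, and can reach a physician at any hour during the 20 weeks.

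Section 8.3 (Recording of adverse events) says: "The following signs and symptoms will be solicited at all visits: itching, fever (by examination), rash, urticaria", with further symptoms listed. It also provides for recording when a volunteer reports something between visits.

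Section 8.7 allows the study to be discontinued if more than half of a dose group have a related grade 3 event "persisting at grade 3 for >48 hours during the 20 weeks follow-up".

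**The concern.** Without a thermometer reading, a fever has no grade under the stated scale. Three parts of the plan need that grade at times when no reading is scheduled.

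- Soliciting fever by examination at all visits does not fit with ending the routine reading at week 12.
- The reporting duty asks volunteers to recognise a grade 2 or 3 event. For fever this means knowing whether the temperature exceeds 38.0 °C, and the protocol does not say how they would know.
- The stopping rule asks whether grade 3 has persisted beyond 48 hours, while scheduled readings are a week apart.

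Fever is prominent in the protocol's descriptions of acute schistosomiasis syndrome (sections 11.3 and 13.1). Section 13.1, item i, says antigen is in principle tested retrospectively, so clinical monitoring carries the real-time safety signal. Section 13.2 has the safety committee review all safety data before escalation. Missed or misgraded fevers would affect a primary endpoint, that review and the fever component of the stopping rule.

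**Working it through.** The plan states no figure on this point, so there is none to reproduce. The check is a count of visits and a simple capture calculation.

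**Visits with and without a routine temperature** (section 8.3 and Figure 3; week 12 taken as included)
- Follow-up visits to week 20: weeks 1 to 16, 18 and 20, so 16 + 2 = 18.
- With a scheduled temperature: weeks 1 to 12, so 12.
- Without: 18 − 12 = 6 (weeks 13, 14, 15, 16, 18, 20).
- Weeks of the stopping window after the last routine reading: 20 − 12 = 8.
- The one-year visit also has no reading but lies outside the stopping window, so it is not counted.

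**Fit with the protocol's own natural history** (section 13.1, item b)
- Acute schistosomiasis syndrome is described as an illness "which occurs three to ten weeks after infection", with most patients recovering after 2 to 10 weeks.
- An episode starting at week 10 could thus end anywhere from week 10 + 2 = 12 to week 10 + 10 = 20. Onset falls inside the measured period, but the tail of a late episode need not.
- Escalation takes place 10 weeks after infection (section 9.5). The week-12 cut-off therefore does not affect that decision for the same group. The lack of a between-visit method does.

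**Capture from visit readings alone** (assumptions: visits 7 days apart, onset random relative to visits, fever continuous for D days)
- Probability that at least one visit reading falls in the episode = min(1, D/7).
- Probability that two consecutive visit readings both fall in it = max(0, min(1, (D − 7)/7)).

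| Fever duration D (days) | At least one reading | Two consecutive readings |
|---|---|---|
| 2 | 2/7 = 0.29 | 0 |
| 3 | 3/7 = 0.43 | 0 |
| 5 | 5/7 = 0.71 | 0 |
| 7 | 1.00 | 0 |
| 10 | 1.00 | 3/7 = 0.43 |
| 14 | 1.00 | 7/7 = 1.00 |

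A single reading shows a grade but not a duration. On these assumptions, visit readings alone cannot show persistence beyond 48 hours for a fever of a week or less. The first column is a lower bound on total capture, because unscheduled contacts add to it. Figure 3 gives a 3-day visit deviation, so real spacing will vary around 7 days.

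**The case against.** The strongest reply is that the protocol does collect data between visits. The diary, the reporting duty, the physician on call, between-visit recording and additional diagnostics at the physician's discretion all allow a fever to be measured when it occurs. Section 9.2.4 gives tympanic measurement as a method and does not restrict it to visits. A thermometer may be provided for in the diary or the volunteer information, which are not shown. This stands: a reader might infer that fever cannot be ascertained at all, and the documents do not support that. What remains is that these channels carry reports, and the protocol does not say how the temperature itself is obtained.

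Other points also limit the concern.

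- Figure 3 marks a clinical evaluation at every visit, and section 8.3 allows a focused examination when the physician finds it necessary. A temperature after week 12 is possible; only the routine reading lapses.
- Section 11.3 expects protracted fever of low to medium grade. Long fevers are more likely to meet a weekly reading, and on the model above a 14-day fever meets two. Misgrading around 38.0 °C may be commoner than a missed stop.
- Section 9.2.4 asks for the diagnosis to be recorded in place of individual signs where one is established, so some fevers would be absorbed into an acute schistosomiasis syndrome entry.
- The stopping rule covers all related grade 3 events, is permissive, and sits beside separate routes through the safety committee, the investigator and the ethics committee. A reader might infer that it is unworkable. Non-fever events are graded by impairment and can be dated from the diary, so only the fever component is affected.
- A reader might infer that every error makes a dose look safer. Missed fevers would, but a fever graded by impairment for want of a reading could err in either direction.
- Fever is not among the praziquantel side effects listed in sections 7.1 and 11.3, and the stopping rule counts only events related to the cercariae. The week-12 treatment therefore adds little to the argument.

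**Conclusion.** The concern holds as an inconsistency in how fever is measured. The grading scale requires a temperature; the routine schedule supplies one only at visits to week 12; fever is solicited at every visit; and the stopping window runs to week 20. Six of 18 visits in that window have no routine reading, and no between-visit method is stated for fevers that volunteers are asked to recognise and report. Fever grade and the fever component of the 48-hour criterion are therefore not reliably ascertained as specified.

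The capture figures of about 0.29 and 0.43 rest on the spacing and onset assumptions and count visit readings alone; actual capture will be higher by an amount the documents do not allow one to estimate. The point should be corrected because it touches a primary safety endpoint and because temperatures never taken cannot be recovered at analysis. It does not invalidate the safety assessment or the stopping rule as a whole.

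**What to change.** Reconcile the two parts of section 8.3 with sections 8.7 and 9.2.4:

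- Delete the week-12 limit, so that tympanic temperature is taken at every visit at least to week 20.
- Add to the existing 20-week diary a self-measured temperature, with date and time, whenever the volunteer feels feverish. Supply a tympanic thermometer if the volunteer materials do not already provide one.
- State that fever grade is the highest reading of the episode, in line with the highest-grade rule already in section 9.2.4, and that persistence is judged from serial dated readings. A maximum alone cannot show duration.
- Leave every grading band and stopping threshold as it is.

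The cost is a low-cost thermometer per volunteer, one diary line and a wording amendment. More mild fevers will be recorded, which should be borne in mind when comparing with the earlier male-cercariae study if temperatures were collected differently there.
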